## 3.10 Sample size Determination

Although the overall aim during data analysis will be to combine participants across all the three country sites, it is recognized that: a) there will most likely be baseline differences across the country sites reflecting the different population characteristics between the countries; and, b) each site will want to analyze data from their site-specific arms. Thus the sample was calculated such that differences between the trials arms in regard to primary outcomes can be detected at each study site separately when desired.

The sample size for this trial has been determined based on the primary hypothesis that by the end of follow-up, the “facility plus community” arm will be superior to the “facility alone” arm, and the current practice arm in Uganda, with respect to: a) mean HbA1c readings among participants with pre-diabetes, and b) the proportion of participants with diabetes with controlled blood sugar levels.

*Sample size for participants with pre-diabetes*

With the aim of being able to detect an average difference between any two trial arms, in mean HbA1c by month 12 of at least 3 mmol/mol (effect size), with a standard deviation of 2.5 mmol/mol in the intervention arm, and a standard deviation of 2.5 mmol/mol in the comparison (control) arm; the required sample size before adjusting for clustering, at an 80% power and 5% level of significance is 34 participants per arm. For this first stage calculations, we used the formula as described in Hayes and Bennett (1999) [Hayes et al. 1999] for a continuous outcome:

$$Initial sample size(n_{i})=\left[ \frac{\left( Z_{\alpha/2}+Z_{\beta} \right)^{2}*\left( \sigma_{0}^{2}+\sigma_{1}^{2} \right)}{\left( \mu_{0}-\mu_{1} \right)^{2}} \right]$$

where: $Z_{\alpha/2}$ = standard normal distribution value at $\alpha$ level of significance

= standard normal distribution value at level of significance

[figure not shown]

[figure not shown]

[figure not shown]

[figure not shown]

$\alpha$ = level of significance

= type 2 error, for which (1-$\beta$) is the power of the study to detect the desired effect size

[figure not shown]

[figure not shown]

$\sigma_{0}^{2}$ = variance of outcome variable (HbA1c) at month 12 in the comparison (control) arm

$\sigma_{1}^{2}$ = variance of outcome variable (HbA1c) at month 12 in the intervention arm

$\mu_{1}$ = mean value of outcome variable (HbA1c) at month 12 in the intervention arm

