$\mu_{0}$ = mean value of outcome variable (HbA1c) at month 12 in the comparison (control) arm

$\left( \mu_{0}-\mu_{1} \right)$ = minimum effect size to be detected

[figure not shown]

[figure not shown]

The necessary sample size for a cluster randomized trial depends on the variation in the intervention effects between the arms, and the clustering due to trial arm allocation (which reduces the variance of the difference between the arms), and the correlation between the repeated observations in each participant. Given that we have a fixed number of health facilities (clusters), to adjust for clustering we used a formula for fixed number of clusters and fixed number of participants within clusters as described in Hemming et al (2011) page 19 [Hemming et al. 2011].

$$Sample size per cluster=\frac{n_{i}*k*\left( 1-\rho\right)}{\left( k-n_{i}*\rho\right)}$$

where: $n_{i}$ = initial sample size

$k$ = number of clusters

= inter-cluster correlation

[figure not shown]

[figure not shown]

It is important to note that each site will be using different numbers of clusters; specifically Uganda will be working in 9 clusters, Sweden in 4 clusters, whereas South Africa will be working in 2 clusters. Thus different inter-cluster correlation (ICC) coefficient values are expected. We were unable to find published literature providing estimates for ICC coefficients for HbA1c among persons with pre-diabetes. We therefore explored various values of ICC coefficients for each site, and used values that provided the highest sample sizes to detect the desired effect size. For Uganda we used an ICC value of 0.200 to obtain a sample size of 112 participants, for South Africa we used an ICC value of 0.044 to obtain a sample size of 129, whereas for Sweden we used an ICC value of 0.06 to obtain a sample size of 79; all per study arm. For Sweden, there will be a further interest to compare the primary outcome of interest between immigrant participants of non-European origin versus immigrant participants of European origin. In order to allow for this sub-analysis, the sample size of 79 for Sweden was doubled to 158 to enable detection of the same effect size between immigrant participants of non-European origin versus immigrant participants of European origin.

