Further, we project a loss to follow-up of up to 10% over the 12 months follow up, thus the sample sizes obtained were accordingly adjusted upwards by 10%. Table 16 (a) provides a summary of the estimates used, and the sample size estimates obtained.

Table 16 (a): Parameter value estimates used in sample size calculations for participants with pre-diabetes

| **Parameter** | **Estimate** | | |
| --- | --- | --- | --- |
| Level of significance (α) | 5% | | |
| Power (1-β) | 80% | | |
| Primary outcome of interest | Mean change in HbA1c reading | | |
| Standard deviation (σ), of mean change in HbA1c | 2.5 | | |
| Minimum anticipated difference between arms, in primary outcome by month 12 | $\left( \mu_{0}-\mu_{1} \right)$ =  5 mmol/mol | | |
| Required sample size per arm, before adjusting for clustering (*n_i_*) | 34 | | |
|  | Uganda | South Africa | Sweden |
| Number of clusters | 9 | 2 | 4 |
| Inter-cluster correlation (ρ) | 0.200 | 0.044 | 0.070 |
| Sample size per arm, after adjusting for clustering (n) | 112 | 129 | 158 |
| Sample size per arm, after further adjusting for estimated loss to follow-up of 10% | 124 | 142 | 174* |

* *For Sweden, at least 87 participants with pre-diabetes will need to be immigrants of non-European origin, and at least 87 participants with pre-diabetes will need to be immigrants of European origin*

*Sample size for participants with diabetes*

A prospective cohort study among patients with diabetes in the United Kingdom showed that people with type 2 diabetes who reduce their HbA1c level by 1% are: a) 19% less likely to suffer cataracts, b) 16% less likely to suffer heart failure, and c) 43% less likely to suffer amputation or death due to peripheral vascular disease [Stratton et al. 2000]. Therefore among participants with diabetes, we aim at reducing their plasma glucose levels by month 12. A participant with diabetes will be defined as having had their plasma glucose reduced if:

1. Their HbA1c reading at month 12 is reduce to below 53 mmol/mol, or
2. Their HbA1c reading at month 12 is 5 mmol/mol below their baseline reading.

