Thus we will aim at maximizing the proportion of participants with diabetes whose blood sugar levels has been reduced, per the criteria defined above. We aim at being able to detect a difference of at least 2% in the percentage of participants with diabetes with reduced plasma glucose levels by month 12 between the trial arms (effect size). The required sample size before adjusting for clustering, at 80% power and 5% level of significance is 58 participants per arm. We have also assumed that in the intervention arm we shall attain reduction in plasma glucose per the criteria given above, in 30% of participants with diabetes (P_1_= 0.3). For this first stage calculations, we used the formula as described in Hayes and Bennett (1999) [Hayes 1999] for proportions, that is:

[figure not shown]

where: $n_{i}$ = initial sample size (58)

$P_{0}$ = Proportion of participants with diabetes in the comparison (control) arm, whose plasma glucose levels are controlled by month 12 (32%)

$P_{1}$ = Proportion of participants with diabetes in an intervention arm, whose plasma glucose levels are controlled by month 12 (30%)

For an estimate of inter-cluster correlation (ICC) among individuals with diabetes, we found only two publications of cluster randomized trials reporting ICC estimates among diabetes patients, one by Littenberg et al (2006) in which they report an inter-cluster correlation (ICC) coefficient for HbA1c among patients with diabetes of 0.055 [Littenberg et al. 2006]; and another by Singh et al (2015) in which they report an ICC coefficient of 0.091 [Singh et al. 2015]. We use some of these estimates. For Uganda we used an ICC value of 0.0.091 to obtain a sample size of 128 participants, for South Africa we used an ICC value of 0.020 to obtain a sample size of 136, whereas for Sweden we also used an ICC value of 0.020 to obtain a sample size of 81; all per study arm.

Once again for Sweden, there will be a further interest to compare the primary outcome of interest between immigrant participants of non-European origin versus immigrant participants of European origin. In order to allow for this sub-analysis, the sample size of 81 for Sweden was doubled to 162 to enable detection of the same effect size immigrant participants of non-European origin versus immigrant participants of European origin.

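### The pre-diabetes starting size of 34 per arm follows from neither stated effect size (the protocol's formula gives 11 or 4), so the detectable difference cannot be traced; some Swedish figures and the overall N also need correcting

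*Protocol*

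**What the plan says.** All of this is in Protocol Section 3.10.

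- **Pre-diabetes, text.** The difference to detect is "in mean HbA1c by month 12 of at least 3 mmol/mol (effect size), with a standard deviation of 2.5 mmol/mol"; the same SD is assumed for both arms. The size before clustering, "at an 80% power and 5% level of significance is 34 participants per arm", is attributed to a two-means formula using Z at α/2. The variances in that formula are defined as those of HbA1c at month 12.
- **Pre-diabetes, Table 16(a).** The row "Minimum anticipated difference between arms, in primary outcome by month 12" shows 5 mmol/mol. The SD is again 2.5, now labelled as the SD of mean change, and n_i is again 34.
- **Clustering.** The site sizes use n_i·k·(1−ρ)/(k−n_i·ρ), and "Uganda will be working in 9 clusters, Sweden in 4 clusters, whereas South Africa will be working in 2 clusters". The text says that "for Sweden we used an ICC value of 0.06 to obtain a sample size of 79" per arm, while Table 16(a) gives the Swedish ICC as 0.070.
- **Swedish diabetes.** In the text, "the sample size of 81 for Sweden was doubled to 162". Table 16(b) prints 81, and 90 after loss to follow-up. Its footnote asks for at least 90 participants of non-European and 90 of European origin. The note to Figure 15 says 179, described as 90 plus 90.
- **Total.** Figure 15 gives an overall N of 1997 above site boxes of 795, 584 and 706.

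**The concern.** Two different target differences share one SD and one sample size, so at most one can be the basis of the 34. In fact neither is. HbA1c at month 12 in pre-diabetes is a primary outcome, and Section 3.10 says each site was sized to show arm differences on its own. All three sites' pre-diabetes targets start from this number. If its inputs cannot be recovered, a reader cannot say what difference the trial is designed to detect or judge a null result against it.

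The label on the SD adds to this. The SD of a month-12 value and the SD of a change from baseline are different quantities, and the text and the table disagree on which one is meant.

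The Swedish figures and the headline total are smaller matters. They are direct contradictions in numbers that staff will copy from the document.

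**Working it through.** **Inputs (Section 3.10):** SD 2.5 in both arms; difference 3 mmol/mol (text) or 5 mmol/mol (Table 16(a)); two-sided 5%; power 80%; n_i = 34; k = 9, 2 and 4 for Uganda, South Africa and Sweden; ICC 0.200, 0.044, and 0.06 (text) or 0.070 (table); 10% uplift for loss to follow-up.

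**1. Attempt to reproduce 34.** The formula is n_i = (Z_α/2 + Z_β)²(σ₀² + σ₁²)/(μ₀ − μ₁)², with (1.960 + 0.842)² = 7.849 and σ₀² + σ₁² = 6.25 + 6.25 = 12.5.

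- Difference 3: 7.849 × 12.5 / 9 = 10.90, so 11 per arm.
- Difference 5: 7.849 × 12.5 / 25 = 3.92, so 4 per arm.

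Other readings do not give 34 either:

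| Variant | Difference 3 | Difference 5 |
|---|---|---|
| One-sided 5%, 80% power | 9 | 4 |
| Two-sided, 90% power | 15 | 6 |
| Two-sided, 95% power | 19 | 7 |
| t-based, 80% power | 12 | 6 |
| SD 2.5 × √2 | 22 | 8 |
| SD 5 | 44 | 16 |

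**2. What 34 would imply.**

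- At SD 2.5: difference = √(7.849 × 12.5 / 34) = 1.70 mmol/mol.
- At difference 3: SD = √(34 × 9 / (2 × 7.849)) = 4.42.
- At difference 5: SD = √(34 × 25 / (2 × 7.849)) = 7.36.

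**3. Was 34 really carried forward?** Using the printed clustering formula and the printed k:

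- Uganda: 34 × 9 × 0.800 / (9 − 6.8) = 111.3, so 112, as printed.
- South Africa: 34 × 2 × 0.956 / (2 − 1.496) = 128.98, so 129, as printed.
- Sweden, ICC 0.070: 34 × 4 × 0.93 / (4 − 2.38) = 78.1, so 79, as printed.
- Sweden, ICC 0.06: 34 × 4 × 0.94 / (4 − 2.04) = 65.2, so 66, not 79.

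With the 10% uplift, 112 × 1.1 = 123.2, 129 × 1.1 = 141.9 and 158 × 1.1 = 173.8 give the printed 124, 142 and 174. So 34 is the number actually used, and 0.070 is the Swedish ICC actually used.

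**4. How far the starting size matters.** With n_i = 11 and the Table 16(a) ICCs, the same formula gives:

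- Uganda: 79.2 / 6.8 = 11.6, so 12.
- South Africa: 21.032 / 1.516 = 13.9, so 14.
- Sweden before doubling: 40.92 / 3.23 = 12.7, so 13.

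The printed sizes are 112, 129 and 79. This takes k as the protocol prints it; whether k is the right count is a separate question and nothing here rests on it.

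**5. Swedish diabetes, taken from the printed n_i of 58.** 58 × 4 × 0.98 / (4 − 1.16) = 80.06, so 81. Then 81 × 1.1 = 89.1, so 90, and twice that is 180. Doubling before the uplift gives 162 × 1.1 = 178.2, so 179.

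**6. Total.** 3 × 265 + 2 × 292 + 2 × 353 = 795 + 584 + 706 = 2085. The printed 1997 is 88 lower, which is 88/2085 = 4.2%. With 180 for Swedish diabetes the total is 2087. With Table 16(b)'s undoubled 90 it is 795 + 584 + 2 × 264 = 1907. None of these gives 1997.

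**The case against.** The arithmetic is not open to dispute, and the conflicting figures stand in readable text, so they are not extraction faults. The case on the other side concerns what follows from them, and much of it stands.

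- **Direction.** A reader might infer that the pre-diabetes comparison is underpowered. The documents do not show that. On the stated inputs 34 exceeds the requirement; in the unclustered formula it gives 99.9% power for 3 mmol/mol at SD 2.5.
- **Recruitment targets.** A reader might infer that sites do not know how many to recruit. That does not follow. The per-arm numbers agree with their parts (265 = 124 + 141, 292 = 142 + 150, 353 = 174 + 179), and the site boxes are exact multiples of them. Only the headline sum is wrong.
- **Swedish diabetes.** The footnote to Table 16(b) already carries the doubling, and 179 against 90 + 90 is a matter of when one rounds. What remains is an undoubled column, inconsistent with Table 16(a), which does show the doubled figures.
- **Which input is wrong.** It is tempting to conclude that 34 is right and to supply 1.7 mmol/mol, or an SD of 4.4, to match. Neither value appears anywhere in the protocol, and nothing in it settles whether the difference, the SD or the 34 is at fault.

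The central point survives: two stated differences, one stated SD, and a sample size that follows from neither.

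**Conclusion.** The concern holds as a traceability error in the sizing of a primary outcome. On the stated inputs, 34 is about 3 times what the formula requires at 3 mmol/mol (34/11) and about 8 times at 5 mmol/mol (34/4). The 112, 129 and 79 all descend from it. The conclusion rests only on the printed formula, SD, power and two-sided 5% level, and no plausible variation of these recovers 34.

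The finding is that the detectable difference is undocumented, not that power is lacking. If the true SD is near 4.4 (for 3 mmol/mol) or 7.4 (for 5 mmol/mol), 34 would be right and the stated SD wrong. If SD 2.5 is right, the sizes are larger than either stated difference needs at this step.

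The remaining items are minor: the Swedish ICC conflict (66 against 79 per arm before doubling), the undoubled column in Table 16(b), and an overall N that is 88 too low against its own boxes.

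**What to change.** **Main change.** State in both the text and Table 16(a) the single difference and SD actually intended, with their source. Say whether the SD is that of HbA1c at month 12 or of change from baseline. Recompute n_i and the three clustered sizes from those inputs. If the enrolment targets are to be kept, restate the difference or the power that they deliver; do not choose inputs so that 34 comes out.

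**Minor corrections.**

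- Give one Swedish pre-diabetes ICC in text and table. The printed 79 follows from 0.070; 0.06 would give 66.
- In Table 16(b), show the doubled Swedish diabetes figures: 162, and then 179 or 180 after loss to follow-up. Use the same choice in Figure 15.
- Correct the overall N to the sum of the boxes: 2085 as printed, or 2087 with 180.

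**Cost.** The minor corrections are clerical. If the targets are kept, the main change is a rewritten paragraph, a corrected table and a short recalculation. If the sizes are recomputed from the intended inputs, pre-diabetes enrolment may change, and the amount cannot be known until those inputs are stated.

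### The clustering adjustment in section 3.10 enters each site's total clusters (9, 2, 4) in a per-arm formula, so 80% power at each site separately does not follow from the protocol's own inputs

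*Protocol*

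**What the plan says.** Section 3.10 sets a site-level goal: "the sample was calculated such that differences between the trials arms in regard to primary outcomes can be detected at each study site". For pre-diabetes, "the required sample size before adjusting for clustering, at an 80% power and 5% level of significance is 34 participants per arm"; for diabetes the corresponding figure is 58 per arm. Both then go through a fixed-cluster formula, n = n_i × k × (1 − ICC) / (k − n_i × ICC), in which k is defined only as the number of clusters. On its value the protocol says "specifically Uganda will be working in 9 clusters, Sweden in 4 clusters, whereas South Africa will be working in 2 clusters", and Tables 16(a) and 16(b) enter 9, 2 and 4. The adjusted figures (112, 129 and 79 for pre-diabetes; 128, 136 and 81 for diabetes; Uganda, South Africa, Sweden) are described as per study arm. The Swedish figures are then doubled in the text to 158 and 162 for a comparison by origin, although Table 16(b) keeps 81.

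Section 3.1 allocates each facility cluster to one arm. Section 3.2 gives Uganda three arms and the other two countries two each.

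For pre-diabetes ICCs the protocol found no published values, explored several and "used values that provided the highest sample sizes to detect the desired effect size". For diabetes it cites 0.055 and 0.091, uses 0.091 in Uganda and 0.020 in Sweden, and "for South Africa we used an ICC value of 0.020 to obtain a sample size of 136".

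**The concern.** Everything in the formula except k is per arm. Entering the site total gives each arm two or three times the clusters it will have, which understates the design effect. In Uganda, 9 clusters in each of three arms would mean 27 facilities; section 3.4.1 counts 23 level III and IV centres in the two districts and selects 9.

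The statement at stake is that site comparisons are adequately powered. Section 3.13.1 makes site-specific comparison the fallback if pooling proves impossible. A null result at one site could then be read as absence of effect when the comparison had little chance of finding one.

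**Working it through.** **Inputs.** n_i = 34 and 58 per arm, two-sided 5%, 80% power, and the ICCs of Tables 16(a) and 16(b). The cluster codes in the data collection tools (South Africa 1-2, Sweden 1-4, Uganda 1-9) confirm that 9, 2 and 4 are site totals. Equal allocation gives k = 3, 1 and 2 per arm.

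**Where the formula comes from.** With m = n/k participants per cluster, n = n_i × [1 + (m − 1) × ICC]. Solving for n gives the protocol's expression. Since n and n_i are per arm, k is clusters per arm. The protocol labels the result as a size per cluster, but it is a size per arm.

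**Reproducing the stated figures, then correcting k:**

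| Cell | n_i | ICC | Total k: result | Stated | k per arm | k − n_i × ICC | Corrected n |
|---|---|---|---|---|---|---|---|
| Pre-diabetes, Uganda | 34 | 0.200 | 111.3 | 112 | 3 | 3 − 6.8 = −3.8 | none |
| Pre-diabetes, South Africa | 34 | 0.044 | 129.0 | 129 | 1 | 1 − 1.496 = −0.50 | none |
| Pre-diabetes, Sweden | 34 | 0.070 | 78.1 | 79 | 2 | 2 − 2.38 = −0.38 | none |
| Diabetes, Uganda | 58 | 0.091 | 127.5 | 128 | 3 | 3 − 5.278 = −2.28 | none |
| Diabetes, South Africa | 58 | 0.020 | 135.3 | 136 | 1 | 1 − 1.16 = −0.16 | none |
| Diabetes, Sweden | 58 | 0.020 | 80.1 | 81 | 2 | 2 − 1.16 = 0.84 | 58 × 2 × 0.98 / 0.84 = 135.3, so 136 |

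All six stated figures come back with total k. The Swedish pre-diabetes figure needs the ICC of 0.070 in Table 16(a); the 0.06 in the text gives 66. With 0.06 and k = 2 the denominator is 2 − 2.04 = −0.04, still without a solution.

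A negative denominator means that the largest attainable effective sample, k/ICC, is below n_i. In Ugandan pre-diabetes it is 3/0.2 = 15 per arm against 34 needed.

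**Power at the stated n.** Effective size n_eff = n / [1 + (n/k − 1) × ICC]. Noncentrality = (1.960 + 0.842) × √(n_eff/n_i). Power is Φ(noncentrality − 1.96), or from a noncentral t on 2(k − 1) df.

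| Cell | n | n_eff | Normal | t (df) |
|---|---|---|---|---|
| Pre-diabetes, Uganda | 112 | 13.55 | 42% | 28% (4) |
| Pre-diabetes, South Africa | 129 | 19.45 | 56% | none (0) |
| Pre-diabetes, Sweden | 79 / 158 | 21.38 / 24.46 | 60% / 66% | 25% / 28% (2) |
| Diabetes, Uganda | 128 | 26.71 | 48% | 31% (4) |
| Diabetes, South Africa | 136 | 36.76 | 61% | none (0) |
| Diabetes, Sweden | 81 / 162 | 45.25 / 62.31 | 70% / 83% | 30% / 37% (2) |

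**Pooled facility + community against facility only, stratified by country.** The clusters are 6 + 2 + 4 = 12, less three strata and one arm effect, so 8 df. Effective sizes add across countries.
- Pre-diabetes, stated ICCs: 13.55 + 19.45 + 24.46 = 57.46, power about 89%.
- Diabetes, stated ICCs: 108.72 (Sweden 81) or 125.78 (Sweden 162), 92% to 95%.
- Diabetes, ICC 0.055 everywhere: 80.56 or 85.03, 82% to 84%.
- Diabetes, ICC 0.091 everywhere: 54.58 or 56.52, 66% to 68%.

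**The case against.** The strongest reply is that these power figures are tied to n_i = 34 and 58, which do not follow from the stated effects. A difference of 3 mmol/mol with SD 2.5 needs 2 × 6.25 × 7.849 / 9 = 10.9, so 11 per arm; the 5 mmol/mol in Table 16(a) needs 4. With n_i = 11 and k = 3, 1, 2 the formula has solutions at all three sites (about 33, 21 and 17 per arm), and normal-approximation power at the planned sizes is about 88% in Uganda, 96% in South Africa and 98-99% in Sweden. This stands. A reader might infer that no sample could detect the 3 mmol/mol difference at any site; the documents do not support that. On cluster degrees of freedom, power for that difference is still only about 65% in Uganda and 55-60% in Sweden, with no test in South Africa. For diabetes the mismatch runs the other way: 30% against 32% needs about 8,390 per arm, so the percentages above are far too favourable for that difference.

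Sweden's 2 clusters per arm is also conditional. Sections 3.1 and 3.4.3 make the health centre and its catchment the cluster, whereas section 3.6.3 describes allocating postal-code zones within centres. Uganda and South Africa are unaffected.

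Swedish diabetes at the doubled 162 does reach 80% by the normal approximation, so the shortfall is not universal on that scale.

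Finally, the planned analysis pools sites, and different ICCs by country are a defensible choice. A reader might infer that 0.020 is an error or that one ICC must apply everywhere. The protocol says it expects ICCs to differ, and the cited 0.055 is for HbA1c itself, not for a responder proportion. What remains is that 0.020 lies below both cited values and no range is shown. None of this makes the site total the right k.

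**Conclusion.** The point holds. The six adjusted sample sizes arise only from using site totals as k in a per-arm calculation. With the protocol's own n_i and ICCs, clusters per arm leave five cells without a solution and raise the sixth from 81 to 136, so the site-level claim is unsupported. In South Africa arm and facility are fully confounded, and extra participants cannot repair that.

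The size of the shortfall rests on three assumptions: equal allocation of clusters to arms, health centres as the Swedish clusters, and the effects implied by 34 and 58. The misuse of k itself needs none of the effect assumptions.

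It would go too far to say that the 80% claim can simply move to the pooled comparison. For diabetes it holds at the stated ICCs and at 0.055 but fails at 0.091, and only for the effect implied by 58.

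**What to change.** 1. First reconcile n_i with the stated effects: 3 or 5 mmol/mol with SD 2.5, and 30% against 32%. Every power figure depends on this.
2. In the formula and Tables 16(a) and 16(b), define k as clusters per arm (3, 1, 2), label the result as per arm, and state what the Swedish cluster is, in agreement with sections 3.1, 3.4.3 and 3.6.3.
3. Withdraw the statement that arm differences can be detected at each site separately with 80% power. Report recomputed site power, with the degrees of freedom, and say that South Africa alone supports no between-cluster test.
4. Give pooled power together with its ICC and effect, and show 0.055 and 0.091 as a sensitivity range beside the 0.020 used for South Africa and Sweden.

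The cost is rewriting section 3.10 and two tables, with less favourable site-level power on record. No patients are added.

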Similarly, we project a loss to follow-up of up to 10% over the 12 months follow up, thus the sample sizes obtained were accordingly adjusted upwards by 10%. Table 16 (b) provides a summary of the estimates used, and the sample size estimates obtained.

Table 16 (b): Parameter value estimates used in sample size calculations for participants with diabetes

| **Parameter** | **Participants with Diabetics** | | |
| --- | --- | --- | --- |
| Level of significance (α) | 5% | | |
| Power (1-β) | 80% | | |
| Primary outcome of interest | % of participants with reduced plasma glucose | | |
| Proportion of participants with reduced HbA1c by month 12 in control arm ($P_{0}$) | 30% | | |
| Minimum anticipated difference between arms, in primary outcome by month 12 | $\left( P_{0}-P_{1} \right)$ = 2% | | |
| Required sample size per arm, before adjusting for clustering (*n_i_*) | 58 | | |
|  | Uganda | South Africa | Sweden |
| Number of clusters | 9 | 2 | 4 |
| Inter-cluster correlation ($\rho$) | 0.091 | 0.020 | 0.020 |
| Sample size per arm, after adjusting for clustering (n) | 128 | 136 | 81 |
| Sample size per arm, after further adjusting for estimated loss to follow-up of 10% | 141 | 150 | 90 |

* *For Sweden, at least 90 participants with diabetes will need to be immigrants of non-European origin, and at least 90 participants with diabetes will need to be immigrants of European origin*

Figure 15 summarizes the trial and the sample sizes to be used at each site per study arm.

Figure 15: Schema for the trial

^ф^265 = 124 with pre-diabetes, & 141 with diabetes

^€^292 = 142 with pre-diabetes, & 150 with diabetes

^¥^353 = 174 with pre-diabetes (87 immigrants of European origin plus 87 immigrants of non-European origin),

& 179 with diabetes (90 immigrants of European origin plus 90 immigrants of non-European origin)

Overall total participants

N=1997

Uganda

n=795

South Africa

n=584

Sweden

n=706

Follow-up

Month 3

Month 6

Month 12

Baseline evaluation

Facility only

n=292^€^

Facility+ community

n=292

Facility only

n=353^¥^

Facility+ community

n=353

Facility only

n=265^ф^

Facility+ community

n=265

Control

n=265

Randomization

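### For participants with diabetes, 58 per arm is said to give 80% power for a 2-point difference; 2 points would need about 8,400 per arm, and 58 fits roughly 20 to 25 points

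*Protocol*

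**What the plan says.** Section 3.10 bases the sample size on the hypothesis that facility plus community is superior to facility alone (and to current practice in Uganda). For diabetes the outcome is the proportion of participants whose plasma glucose is reduced, or controlled, by month 12, so a higher proportion is better.

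- Effect: "We aim at being able to detect a difference of at least 2% in the percentage of participants with diabetes".
- Size: "The required sample size before adjusting for clustering, at 80% power and 5% level of significance is 58 participants per arm".
- Intervention arm: success is assumed "in 30% of participants with diabetes (P_1_= 0.3").
- Control arm: the symbol list under the formula defines it as the proportion "whose plasma glucose levels are controlled by month 12 (32"%).
- Table 16(b): the row "Proportion of participants with reduced HbA1c by month 12 in control arm" reads 30%, the difference P0 − P1 reads 2%, and the pre-clustering size again reads 58.

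The 58 is then adjusted for clustering to 128 per arm in Uganda, 136 in South Africa and 81 in Sweden. The text doubles the Swedish figure to 162. The section says the sample was calculated so that differences can be detected at each site separately, although the overall aim is to combine the sites.

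**The concern.** A difference of 2 points near 30% is very small, and a comparison of two proportions at 80% power needs thousands per arm to detect it. A figure of 58 cannot come from those inputs. The 2% is not an isolated misprint: it stands in the prose, in the 32%/30% pair and in the table.

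The two places also disagree on which arm has 30%. In the text the control arm does better than the intervention arm, which contradicts the superiority hypothesis. The table labels the 30% as control, and its P0 − P1 = 2%, read literally, then puts the intervention at 28%, again below control.

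This is the power statement for one of the two outcomes on which the trial is sized. Ethics committees, funders and readers are told that the trial can resolve 2 points when its size corresponds to a difference about ten times as large.

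**Working it through.** **Inputs.** From section 3.10 and Table 16(b): 80% power, 5% significance, a difference of 2 points, rates of 30% and 32% (text) or 30% and 28% (table, read literally), n = 58. The test is taken as two-sided because the formula for the continuous outcome uses Z at α/2. The formula for proportions is an image that is not shown in the copy reviewed, so the standard unpooled form is assumed:

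n = (1.96 + 0.8416)² × [P0(1 − P0) + P1(1 − P1)] / (P0 − P1)², with (1.96 + 0.8416)² = 7.849.

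**Step 1: the stated figure.**
- 30% vs 32%: 7.849 × (0.2100 + 0.2176) / 0.0004 = 8,390.5, so 8,391 per arm. That is 8,391 / 58, or about 145 times the stated size.
- 28% vs 30%: 7.849 × (0.2016 + 0.2100) / 0.0004 = 8,076.5, so 8,077 per arm.
- Variants for 30% vs 32%: pooled 8,394, continuity-corrected 8,493, one-sided 6,612. Across all variants and both pairs the range is about 6,400 to 8,500, so 58 is not reproduced.

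**Step 2: is 58 the number actually used?** The protocol's cluster formula is n·k·(1 − ρ) / (k − n·ρ). With n = 58:
- Uganda (k = 9, ρ = 0.091): 58 × 9 × 0.909 / (9 − 5.278) = 127.5, stated as 128.
- South Africa (k = 2, ρ = 0.020): 58 × 2 × 0.98 / (2 − 1.16) = 135.3, stated as 136.
- Sweden (k = 4, ρ = 0.020): 58 × 4 × 0.98 / (4 − 1.16) = 80.1, stated as 81.

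All three agree after rounding up, so 58 drives the planned sizes. With n = 8,391 the same formula has no solution, because n·ρ is about 764 in Uganda and 168 in South Africa and Sweden, far above k = 9, 2 and 4.

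**Step 3: power for 30% vs 32%** (normal approximation, both tails).

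| Comparison | n per arm | Power |
| --- | --- | --- |
| Before clustering | 58 | 5.6% |
| Planned site sizes, clustering ignored | 128 to 162 | 6.4% to 6.8% |
| Planned site sizes, protocol ICCs | effective 58 to 90 | 5.6% to 6.0% |
| All sites pooled, clustering ignored | 128 + 136 + 162 = 426 | 9.7% |
| All sites pooled, protocol ICCs | effective 207 | 7.2% |

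Effective sizes are n / [1 + (n/k − 1)ρ]: 58.1, 58.1 and, for Sweden at 162, 90.5. They sum to 206.7.

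**Step 4: which difference does 58 fit?**
- 10% vs 30%: 7.849 × (0.09 + 0.21) / 0.04 = 58.9. Power at 58 is 79%.
- 30% vs 55%: 7.849 × (0.21 + 0.2475) / 0.0625 = 57.5, so 58. Power at 58 is 80%.
- For contrast, 30% vs 50% (20 points upward from 30%) has 61% power at 58.

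The detectable difference therefore depends on the base rate.

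**The case against.** The strongest reply is that the 2% is a dropped zero. If the intervention rate is 30%, as the text says, and control is 10%, the formula gives 58.9, the difference is 20 points and the intervention is superior. The design would then be sound and only the wording at fault. This is plausible, but 58.9 should round up to 59, and a control rate of 10% appears nowhere in the document. The rival pair, 30% vs 55%, rounds correctly to 58 and keeps the table's control rate of 30%, but 55% appears nowhere either. What stands is that the intended effect cannot be recovered from the protocol.

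A reader might also infer that the trial can only detect about 25 points. The document does not support that. It holds upward from a 30% base at an effective size of 58. From 10% vs 30% the figure is about 20 points, and if clustering were ignored, 128 to 162 per arm would detect about 17 to 15 points upward from 30%.

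Nor is about 6% the power of the whole trial. It is a site-level figure, which fits the way the trial is sized, but the planned combined analysis would have about 7% to 10%. That is still negligible for 2 points.

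Finally, a reader might fear that a null result would be taken to exclude a 2-point benefit. What a result excludes is shown by its confidence interval, so the case does not rest on that.

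**Conclusion.** The stated power is wrong as written and must be corrected. A 2-point difference needs about 8,391 per arm (8,077 on the table's figures) against the 58 stated, and power for it is about 5.6% at 58 per arm and no more than about 10% on any pooling considered here. The 58, and the site sizes built on it, correspond to a difference of roughly 20 to 25 points depending on the base rate. Separately, text and table conflict on which arm has 30%, and the text's direction contradicts the superiority hypothesis.

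This rests on a two-sided 5% test, the standard two-proportion formula, and the protocol's own cluster counts and ICCs. The choice of formula variant does not matter: none comes near 58. The conclusion does not extend to saying which pair of rates was used, nor that thousands more participants should be recruited. By the protocol's own cluster formula, no number of participants in these clusters would deliver 80% power for 2 points.

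**What to change.** In section 3.10 and Table 16(b):

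1. Delete the claim that a 2% difference can be detected.
2. State the P0 (control) and P1 (intervention) actually used to obtain 58, with the intervention better than control, and with the same values and labels in the text, the symbol list and the table.
3. Restate the detectable difference that 58 per arm, the effective size after clustering, supports: about 20 points if the pair was 10% vs 30% (79% power), or about 25 points upward from 30% (80% power for 30% vs 55%). The sponsor has to say which pair applies; neither should be adopted by default.

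Enrolment need not change, and the work is a correction of wording and table entries. The real cost is that the protocol will state a much less favourable detectable difference. If the sponsor finds that a difference of 20 to 25 points is not what was intended, the question becomes one of design and not only of wording.
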